## 5 STUDY DESIGN

### 5.1 Overall Design

This is a multi-site, stepped wedge cluster randomized controlled trial to evaluate the effect of the PT-AWV intervention on AWV and preventive health services use. The study will take place in 24 primary care practices around the United States (8 community-based, 8 academic, and 8 safety net practices). Recruitment and intervention implementation occur at the practice level. We hypothesize that the intervention will increase uptake of AWVs and use of preventive health services.

The **stepped wedge cluster design** is a pragmatic study design that includes an initial control period in which no clusters receive the intervention. Randomized clusters cross to the intervention condition at regular intervals, and there is a period at the end of the study where all clusters have been exposed to the intervention. Data are collected throughout the study so that each cluster contributes to both the control and intervention periods.[^155-157^](#_ENREF_155) The intervention will be implemented sequentially over 15 months, with 4 clusters of 6 practices each switching from control to intervention every 3 months. For each practice, intervention implementation will occur over a 6-month period. All practices will complete intervention implementation 15 months after the onset of intervention implementation in the first set of practices.

Outcomes for the primary and secondary endpoints will be assessed through EHR data extractions. The DARTNet Institute (co-investigator [name], PhD) will serve as the data coordinating center for the study. Co-investigator [name] at the American Academy of Family Physicians National Research Network (AAFP NRN) will clean, de-identify and create flags to develop analytic datasets. The AAFP NRN has established contracts and agreements with the DARTNet Institute that enable [name] to access DARTNet’s data. [name] will deliver limited datasets to investigators at the University of California, Los Angeles for analyses.

In addition to the procedures described above, we will evaluate implementation and sustainability of the evaluation (tertiary endpoints) by collecting qualitative semi-structured interview data on up to 10 patients per practice after an AWV, and up to 10 clinicians/staff per practice. Clinician and staff interviews will occur immediately, 12- and 24-months post-implementation. Clinicians also will be surveyed at those time points regarding their use of the intervention components (which ones, how often), perceived utility of the components, and barriers and facilitators to intervention implementation.

### 5.2 Scientific Rationale for Study Design

The stepped wedge cluster design is particularly suited to this study because: randomization is at the level of the practice (cluster) rather than at the level of the patient; the design will allow all participating practices to receive the intervention; and it would not be possible to implement the intervention simultaneously at all practices. [^155-157^](#_ENREF_155) Replication of the clinical trial will allow us to evaluate and compare intervention implementation and effects in different types of practice settings.

### 5.3 Justification for Intervention

**Intervention Pilot-Testing.** The investigators successfully pilot-tested the PT-AWV intervention in an organization consisting of 3 practice sites.[^158^](#_ENREF_158) All practices used the eMDs EHR platform. As shown in **Figure 2**, AWV utilization in the past 12 months (across all sites) went from 7% at baseline to 54% eight months post-intervention implementation. Two larger practices each increased AWVs by about 40%, while the smallest practice doubled its AWVs (from 15% to 30%) before dropping to 21%.

**Figure 2.**

**Effect of Practice-Tailored AWV Intervention on rates of AWVs, overall and by practice site**

[figure not shown]

We have found that it is most effective to tailor the intervention to the needs of individual sites, and to allow sites to select the tools they wish to use. The minimum acceptable participation/exposure for intervention implementation is to work with the investigators to develop a practice-specific workflow for performing AWVs and to participate in clinician training sessions on AWV requirements and documentation.

### 5.4 End-Of-Study Definition

Practices reach the end of the study once they complete intervention implementation, contribute the requisite interviews with their patients, clinicians/staff, and contribute final EHR data extractions.

The end of the study is defined as 24 months after intervention implementation has been completed in all participating practices, as shown in the study Schema, [**Section 1.2**](#_1.2_Schema)**.**

## 6 STUDY POPULATION

### 6.1 Inclusion Criteria

***Practices*** must meet the following criteria to be included in the study:

1. Primary care practice
2. Provides care for Medicare patients

***Patients*** must meet all of the following criteria to be included in assessment of outcomes and semi-structured interviews:

1. Have Medicare insurance (and are therefore eligible for an AWV or Initial Preventive Physical Examination (IPPE))
2. Have had at least 1 encounter in the past 12 months at a participating practice

***Clinicians/Staff*** must meet the following criteria to be included in semi-structured interviews:

1. Work at a participating practice
2. Conduct, participate in, schedule, follow up on or supervise procedures for AWVs

Surveys will be given only to clinicians who work at a participating practice and conduct AWVs. Clinicians not currently conducting AWVs will be surveyed if their practice would like them to conduct AWVs.

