### 1.3 Schedule of Activities (SOA)

Major activities for this project **(Table 1)** include:

- Intervention implementation (see [**Section 1.2**](#_1.2_Schema) for timeline of practice participation).
- EHR data extractions (for population-level outcomes assessment).
- Semi-structured interviews with key informants (clinicians/staff) and patients (for evaluation of intervention adoption and implementation). Clinicians/staff will participate in up to 3 sets of interviews. Interviews are not longitudinal and different clinicians/staff may participate at different time points. Patients will participate in a single interview.
- Clinician surveys (for evaluation of intervention adoption).
- Generation of monthly or quarterly feedback reports for each site, based on practice preference.

| **Table 1. Schedule of evaluations for a single practice, starting from intervention implementation** | | | | | | | |
| --- | --- | --- | --- | --- | --- | --- | --- |
| **Evaluation** | **Intervention Implementation Period** | **Post-Implementation Period** | | | | | |
|  | Month 0-6 ± 6 months | Month 7 ± 6 months | Month 12 ± 6 months | Month 24 ± 6 months | July 2025 ± 6 months* | July 2026 ± 6 months* | July 2027 ± 6 months* |
| **Outcome evaluation (population-level)** | | | | | | | |
| EHR data extractions | X |  |  |  | X | X | X |
| **Semi-structured interviews / surveys** | | | | | | | |
| Clinician  surveys |  | X | X | X |  |  |  |
| Clinician/staff  interviews |  | X | X | X |  |  |  |
| Patient  interviews |  | X |  |  |  |  |  |
| **Feedback Reports** | Monthly or Quarterly (based on practice preference) | | |  | | | |
| * EHR data extractions will be performed in the same timeframe for all sites | | | | | | | |

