## 4 OBJECTIVES AND ENDPOINTS

| OBJECTIVES | ENDPOINTS | JUSTIFICATION FOR ENDPOINTS |
| --- | --- | --- |
| Primary |  |  |
| Evaluate the effect of ***the intervention*** (PT-AWV intervention) on:   1. AWV utilization 2. USPSTF and CDC/ACIP-recommended preventive services | **Primary endpoints:**  **AWV utilization** will be assessed by examining: the % of eligible patients completing an AWV (CPT codes G0438, G0439, G0468) or Initial Preventive Physical Examination (IPPE) (CPT code G0422) in the past 12 months.  **Completion of recommended preventive health services** will be measured using a composite preventive health services score (% of total recommended preventive health services that are up to date (of a maximum of 12 recommended services per patient)); measured on the patient-level  **Secondary endpoint:**  **Utilization of individual preventive health services**: % of patients up to date for each preventive health service listed in **Table 2** below. | These endpoints are the primary endpoints of interest.  AWVs mediate fulfillment of clinical endpoints on preventive health services.  Completion of recommended preventive health services can improve population health and reduce mortality. |
| Secondary |  |  |
| Evaluate the effect of ***the intervention*** (PT-AWV intervention) on reducing racial/ethnic disparities in AWV utilization. | As for the primary objective, **AWV utilization** will be assessed by examining: the % of eligible patients completing an AWV (CPT codes G0438, G0439, G0468) or Initial Preventive Physical Examination (IPPE) (CPT code G0422) in the past 12 months. | Secondary endpoints will demonstrate additional effects of the intervention and provide additional information to support the importance of the primary endpoints of AWV and preventive health service utilization |
| Tertiary/Exploratory |  |  |
| Tertiary: Evaluate factors affecting implementation and sustainability of the PT-AWV intervention tools and approaches, implementation strategies, and intervention effect in diverse practice settings. | Facilitators and barriers to intervention adoption and implementation (from semi-structured interviews [with patients, clinicians and staff] and clinician surveys) | These endpoints may suggest further hypotheses for later research and will provide information about causal mechanisms regarding uptake of AWVs |

| **Table 2. Preventive health services, recommended frequency and age, and evidence for use/no use*** | | | |

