Practice CEOs/administration/clinicians will have already agreed for their practice to participate in the study. For clinician/staff interviews, the practice lead will identify relevant parties participating in the process of scheduling, conducting, and following up on AWVs, and will ask them to speak to the study team for the interviews. The practice lead will assist with connecting relevant parties with the study team via email and/or will ask individuals to sign up for open interview slots. Clinicians will receive survey invitations from the study team and/or from their practice lead, practice administrator, or designated practice contact.

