### 9.2 Study Evaluations & Procedures

*EHR data extractions to identify patients for interviews* will be performed to identify eligible patients for semi-structured interviews. Information obtained through the extractions will include patient names, contact information, and date of birth. Extractions will occur within about 1-6 months prior to patient participation in interviews. Clinicians/staff will be identified by practices for participation.

*Clinician/staff interviews* will be conducted via telephone or Zoom videoconferencing and will last approximately 30 minutes. Interviews will be audio-recorded and transcribed verbatim for analysis. Interviews are not longitudinal. Different clinicians/staff may participate at different time points. Interviews will be conducted by a team member with qualitative research expertise.

*Patient interviews* will be conducted via telephone and will last approximately 45-60 minutes. These one-time interviews will be audio-recorded and transcribed verbatim for analysis. Interviews will be conducted by a team member with qualitative research expertise.

*Clinician surveys* will be administered via REDCap or Qualtrics, and will take approximately 5-10 minutes or less to complete. Clinicians will be identified by practice leads for participation.

*Data extractions to assess primary and secondary outcomes*. The DARTNet Institute will serve as the data coordinating center for this study. Organizations will either send DARTNet limited datasets for standardization, or DARTNet will work with the institutions to extract the requisite data to assess study outcomes, which include completion of AWVs and the preventive health measures depicted in [**Section 4**](#_4_OBJECTIVES_AND) (**Table 2**). [name] (co-investigator) will process data and clean the data, help create analytic datasets, and will transfer limited datasets to UCLA for analysis. Data will be extracted at baseline and in July 2025, July 2026, and July 2027.

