#### 10.4.4 Analysis of the Tertiary Endpoints

Tertiary endpoints relate to evaluating intervention adoption and implementation by describing facilitators and barriers to adoption through analysis of semi-structured interviews and clinician surveys.

[name] will guide analysis of semi-structured interviews, with the support of a graduate-level research team member with qualitative research method expertise. Two members of the research team will review transcripts, both independently and together to inductively generate codes relevant to pre-defined measures guided by the RE-AIM framework.[^164-167^](#_ENREF_164) Co-investigators and patient partners will participate in selected analyses to ensure the trustworthiness and robustness of the findings. We will use a template coding approach[^168^](#_ENREF_168) to efficiently identify and segment data relevant to pre-defined measures guided by the RE-AIM framework. Case-based matrices[^169^](#_ENREF_169) will help us to refine and synthesize our understanding of modifiable reasons that emerge as obstacles for implementing and sustaining the PT-AWV intervention, strategies for mitigating obstacles, and practice strengths that facilitate implementation and sustainability. Analyses will compare and contrast themes raised in different practice settings. Analyses will be done in ATLAS.ti, a software program for analyzing qualitative data. Clinician survey responses will be tabulated to determine the intervention components being used. The investigate team will use content analysis to analyze free-text responses to survey questions on barriers and facilitators of AWV completion.

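### Clinician and staff interviews have no route to people who never started, or have entirely given up, AWV work, so the interview evidence on barriers leans towards those still involved

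*Protocol*

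**What the plan says.** Protocol 6.1 sets two conditions for clinician and staff interviews: working at a participating practice, and having a role in AWVs, worded as "Conduct, participate in, schedule, follow up on or supervise procedures for AWVs". Selection repeats that filter. In 6.7, "the practice lead will identify relevant parties participating in the process of scheduling, conducting, and following up on AWVs", and the lead then puts them in touch with the study team or asks them to sign up for slots. Section 9.2 agrees: "Clinicians/staff will be identified by practices for participation".

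The survey rule, also in 6.1, is wider in one respect: "Clinicians not currently conducting AWVs will be surveyed if their practice would like them to conduct AWVs". There is no matching provision for interviews.

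The interviews serve the tertiary objective. The endpoint in Section 4 is "Facilitators and barriers to intervention adoption and implementation", taken from interviews and clinician surveys. Section 10.4.4 says the interview analysis will look for "modifiable reasons that emerge as obstacles for implementing and sustaining the PT-AWV intervention". On timing, 5.1 states: "Clinician and staff interviews will occur immediately, 12- and 24-months post-implementation". Section 1.3 adds: "Interviews are not longitudinal and different clinicians/staff may participate at different time points".

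**The concern.** People who were meant to take up AWV work and did not, or who took it up and gave it up, have the most direct knowledge of why adoption failed or lapsed. If they have no AWV role left, the criterion screens them out of the main qualitative source on exactly that question.

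The selection can grow with time. Because nobody is followed from one round to the next, someone interviewed soon after implementation who later leaves AWV work is not re-contacted by design and no longer meets the criterion. At 12 and 24 months, when sustainability is the question, the eligible group consists of those who stayed involved. Decline is plausible: in the pilot (5.3) the smallest practice rose from 15% to 30% and then fell to 21%. What is at stake is how well the trial can explain such a decline.

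**Working it through.** No arithmetic applies. The check is to set the eligibility rules side by side and ask who can be reached by which route.

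| Person | Interview (6.1, criterion 2) | Survey (6.1) |
|---|---|---|
| Clinician who conducts AWVs, whether or not they use the PT-AWV tools | Eligible | Eligible |
| Clinician who does not conduct AWVs but schedules, follows up or supervises them | Eligible | Only if the practice wants them to conduct AWVs |
| Clinician with no AWV role whom the practice wants to conduct AWVs | No route | Eligible |
| Clinician with no AWV role whom the practice does not, or no longer, want to conduct AWVs | No route | No route |
| Staff member with an AWV role | Eligible | Not surveyed |
| Staff member who was expected to have an AWV role and never started, or who has stopped | No route | No route |

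1. *Reading of the criterion.* The word "currently" does not appear in criterion 2. That the role must exist at the time of interview is inferred from its present tense. The survey sentence in the same section, which makes separate provision for clinicians not conducting AWVs at present, supports that reading.

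2. *Selection.* Sections 6.7 and 9.2 do not widen the criterion. The practice lead is asked to name people who take part in the AWV process. The sign-up slots in 6.7 are still subject to 6.1. The practice payment in 6.7.2 depends partly on supplying the requisite interviews and surveys, with nothing that asks for people outside the process.

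3. *Other interview sources.* Patient interviews do not fill the gap, since 5.1 and 6.7 draw patients from those who completed an AWV.

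4. *The survey as a substitute.* By 9.2 it takes about 5 to 10 minutes or less, against about 30 minutes for a clinician or staff interview. By 10.4.4 its information on barriers is free text. It covers clinicians only, and those not conducting AWVs only on the practice's wish. It narrows the gap for one row of the table and leaves the others as they are.

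5. *Counts.* Section 5.1 allows up to 10 clinicians and staff per practice and does not say whether that is per round or in total. The protocol gives no expected proportion of people who never start or who stop. Neither a number of lost interviews nor a percentage can be derived.

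**The case against.** The case on the other side is substantial, and most of it stands as a limit on the point.

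- *Doing AWVs is not the same as adopting the intervention.* Practices enter with baseline AWV rates of about 16 to 45% (10.2), and the footnote to Table 3 says no particular tool is compulsory. A clinician who does AWVs but ignored or abandoned the PT-AWV tools can be interviewed. A reader might infer that all non-adopters are shut out; the text does not support that.
- *The criterion is broad.* A clinician who no longer conducts AWVs but still schedules, follows up or supervises remains eligible. Only people with no AWV role are excluded.
- *The survey is a named co-source of the endpoint.* It runs at the same three time points and asks about barriers. Its condition fits many of the clinicians of interest, namely those expected to do AWVs who do not. A clinician whose practice assigned AWVs to colleagues is not a failed adopter.
- *Sustained effect is measured elsewhere.* A reader might infer that practices would look better sustained than they are. That does not follow: AWV use at 12, 18 and 24 months is estimated from EHR data on all eligible patients (10.3, 10.4.2), whoever is interviewed, and a fall would show there.
- *Choosing people who know the process is a recognised qualitative approach*, and 1.3 describes interviewees as key informants.

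What the objection does not remove is the missing interview route for clinicians and staff who have no AWV role left. Key informants on why something was not taken up, or was given up, include those who did not take it up or gave it up. The protocol recognises this for the survey and makes no equivalent provision for the interviews.

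**Conclusion.** The point holds as a gap in the sampling for a tertiary, qualitative endpoint. Criterion 2 and nomination by the practice leave no interview route for clinicians or staff who were trained or expected to do AWV work and never started, or who have stopped entirely. The survey is a partial remedy. Interview evidence on barriers to adoption and sustainability is selected towards people still involved in AWVs, most of all at 12 and 24 months.

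The direction of the selection is clear, but its size cannot be stated from the protocol. It depends on how many such people there are, which is not given, and on reading the criterion as applying at the time of interview. If a practice has none, nothing is lost there. The primary and secondary estimates are not touched. This is an inexpensive improvement and does not threaten the trial's main conclusions.

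**What to change.** Extend criterion 2 in 6.1 by a clause such as: *or were trained or expected to work on AWVs, including those who never started or have stopped*. Amend 6.7 and 9.2 to match, so that the study team may also invite such people, where they exist, alongside the practice lead's nominations.

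Two sources can be used to find them: the training attendance and interaction records the study team already keeps (7.4), and the practice's own indication of which clinicians it would like to conduct AWVs, which the survey rule already needs. The second matters because attendance records would miss anyone who never came to training.

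Keep to the existing limit of up to 10 clinicians and staff per practice. No fixed quota is proposed: the protocol offers no basis for one, and a small practice might be unable to fill it. No interviews are added. The cost is an IRB amendment and somewhat harder recruitment, since people who have left AWV work may be less willing to talk about it.

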### 6.2 Exclusion Criteria

Any patient who is deceased will be excluded from assessment of outcomes. For semi-structured interviews, participants will be excluded if they are unable to hear well enough to participate in a telephone interview or if the patient / family member reports that they are too sick.

### 6.3 Inclusion of Vulnerable Participants

#### 6.3.1 Participation of NIH Staff or family members of study team members

Not applicable

### 6.4 Inclusion of Pregnant Women, fetuses or neonates

Not applicable

### 6.5 Lifestyle Considerations

Not applicable

### 6.6 Screen Failures

Screen failures are defined as participants who are interested in participating in semi-structured interviews for this study but do not subsequently enter the study because they do not meet inclusion criteria. These individuals will not be rescreened.

### 6.7 Strategies for Recruitment and Retention

Healthcare organizations/practices will be recruited for the study. For the population cohort, there will be no direct patient recruitment. Outcomes will be extracted from EHRs and will not require active practice or patient participation. Patients will be recruited for one-time, semi-structured interviews. Clinicians and staff will be recruited for three sets of semi-structured interviews and clinicians for three sets of surveys. The interviews and surveys are not longitudinal and different clinicians/staff can participate at different time points. Retention strategies are not needed for this study.

Primary care practices. We have already obtained agreement for participation from 3 large organizations, each comprising at least 30-40 practice sites, and will select up to 8 from each organization to take part in this study.

Patients, clinicians, and staff will be recruited for semi-structured interviews. Clinicians will also be recruited for brief surveys. Informed consent for interviews and surveys will be provided by giving participants a study information sheet prior to the interview and/or obtaining oral consent.

*Patients* may be recruited in several ways:

- Identification of patients completing AWVs through EHR data extractions. The participating practice and/or a proxy designated by the practice (the DARTNet Institute or UCLA) will email or mail potential eligible patients a one-time recruitment letter and information sheet describing the study. Patients will be given the opportunity to phone or email the study team to opt-out of the study. A minimum of 1 week after the letter is sent, a study team member will telephone patients who do not opt-out for follow-up. Patients will receive up to 7 follow-up calls and/or emails, at least 1 week apart, up to 16 weeks after the letters are sent. Inquiries will be handled by the study team.
- Office staff and/or clinicians will invite patients to participate after they complete an AWV, by handing them an information flyer describing the interviews. The flyer will be used as the recruitment script.
- Office staff and/or clinicians will identify patients who previously completed an AWV and will invite them to participate in the study.

*Clinicians / staff*

Practice CEOs/administration/clinicians will have already agreed for their practice to participate in the study. For clinician/staff interviews, the practice lead will identify relevant parties participating in the process of scheduling, conducting, and following up on AWVs, and will ask them to speak to the study team for the interviews. The practice lead will assist with connecting relevant parties with the study team via email and/or will ask individuals to sign up for open interview slots. Clinicians will receive survey invitations from the study team and/or from their practice lead, practice administrator, or designated practice contact.

